### Sample size {14}

Studies that applied the techniques to other populations were analyzed to estimate the percentage of improvement in urinary symptoms after application of TNES and PSES. The studies of Malm-Buatsi et al. [26], Monteiro et al. [15], and Kabay et al. [27] were analyzed. Thus, considering a confidence of 99%, a power of the test of 90%, considering the proportion of patients who had improvement after TNES of 69% (PA = 0.69) and patients who had improvement after PSES of 13% (PB = 0.13), the sample size for each group was 22 women. To calculate the sample, Bioestat 5.0 software was used [28].

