## Assignment of interventions: allocation

### Sequence generation {16a}

Participants will be randomized in a 1:1 ratio to the TPES or PSES group by computer-generated random numbers.

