## Statistical methods

### Statistical methods for primary and secondary outcomes {20a}

Statistical Package for the Social Sciences (SPSS Statistics version 23) software will be used in the statistical analysis. The Shapiro-Wilk test will be initially applied to assess data normality. Data will be described as the mean (standardized deviation) for normally distributed continuous variables, median (interquartile range) for continuous variables without normal distribution, and frequency (percentage) for categorical variables.

For parametric data, comparison between the groups will be carried out using the analysis of variance (ANOVA) test. Significance values lower than 0.05, at the 95% confidence interval, will be interpreted as statistically significant. The clinical relevance of recorded values will be confirmed through effect-size calculations (Cohen’s *d*) based on significant differences. The following effects will be taken into account: 0.00 to 0.49, low; 0.50 to 0.79, medium; and above 0.80, high [32]. The intention-to-treat analysis will be carried out [31].

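### Cohen's d is planned only for significant differences, so with 22 women per arm small-to-moderate between-group effects will be overstated on average and non-significant ones left without an effect size

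*Protocol article*

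**What the plan says.** The protocol article, Statistical methods {20a}, compares the groups by ANOVA for parametric data and calls a p-value below 0.05 significant. It then says "The clinical relevance of recorded values will be confirmed through effect-size calculations", names Cohen's d, and limits the calculation with the words "based on significant differences". The resulting d is graded "0.00 to 0.49, low; 0.50 to 0.79, medium; and above 0.80, high". The section does not say which SD standardises d. It also leaves open whether ANOVA is applied to final scores, to change scores or to a group-by-time term.

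Three other sections matter here:

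- Sample size {14}: "the sample size for each group was 22 women".
- Objectives {7}: the authors expect improvement in both groups and no difference between them.
- Outcomes {12}: the primary outcome is the change in ICIQ-SF, a score from 0 to 21, from baseline to final evaluation.

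**The concern.** The rule makes statistical significance the entry ticket for an effect size and then uses that effect size as evidence of clinical relevance. Three things follow.

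- In a small trial only large observed differences pass the filter. The d values that survive are a selected set and tend to be too big when the true effect is small or moderate.
- The grading scale starts at zero, but the filter removes its lower end. A scale that can return only its upper grades is a weak check on relevance.
- In the outcome the authors predict, no difference, the rule usually returns no between-group effect size. That is where a reader most needs the size of the difference and its precision.

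There is also a conceptual problem. Cohen's d divides a difference by the spread of the sample. It does not say whether a change of so many ICIQ-SF points matters to a patient, so it cannot by itself establish clinical relevance.

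**Working it through.** **Inputs.** n = 22 per arm, from Sample size {14}. Equal allocation, from Sequence generation {16a}: "Participants will be randomized in a 1:1 ratio". Analysis threshold 0.05, from {20a}; the F test for two groups is equivalent to a two-sided t test.

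**The plan's own figure.** Planning inputs are 69% against 13% improved, with 99% confidence and 90% power. The mean proportion is 0.41. Two-sided without continuity correction:

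n = [2.576 × √(2 × 0.41 × 0.59) + 1.282 × √(0.69 × 0.31 + 0.13 × 0.87)]² / 0.56² = (1.792 + 0.733)² / 0.3136 = 20.3, rounded up to 21.

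With continuity correction the two-sided result is 24 and the one-sided result is 22. The stated 22 is reproduced within that range, so 22 per arm is a sound basis for what follows.

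**Smallest |d| that can be significant.** With d on the pooled SD of the variable tested, t = d / √(2/n), so

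|d| minimum = t(0.975, 42) × √(2/22) = 2.018 × 0.3015 = 0.608 (0.598 with Hedges' correction).

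This lies above the whole low class and also cuts off the part of the medium class from 0.50 to 0.60. Losses raise it, to 0.640 at 20 per arm and 0.677 at 18. About 32 to 33 per arm would be needed for a d near 0.50 to be significant.

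**Average reported |d| after the filter.** Results of 400,000 simulated trials per true d, normal data, 22 per arm, keeping those with p<0.05:

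| True d | Share significant | Mean abs(d) if significant | Significant estimates below true d |
|---|---|---|---|
| 0 | 5% | 0.74 | – |
| 0.2 | 10% | 0.76 | 0% |
| 0.3 | 16% | 0.78 | 0% |
| 0.5 | 37% | 0.83 | 0% |
| 0.8 | 74% | 0.96 | 31% |
| 1.0 | 90% | 1.08 | 44% |
| 1.5 | 99.8% | 1.53 | 49% |

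The ratios to the truth are 0.76/0.2 = 3.8, 0.78/0.3 = 2.6 and 0.83/0.5 = 1.7. At a true d of 0.8 the excess is 0.955 − 0.8, about 0.15. At 1.5 the mean without any filter is also 1.53, so the filter adds nothing there.

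**Hand check at a true d of 0.5**, treating the SD as known: the cut-off lies (0.608 − 0.5)/0.3015 = 0.36 standard errors above the truth. The truncated-normal mean is 0.5 + 0.3015 × 0.374/0.359 = 0.81, close to the simulated 0.83.

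**The predicted case.** With no true difference, 5% of comparisons are significant, so about 95% yield no between-group d. The few that do yield one average 0.74.

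**How far the 0.61 floor depends on the definition of d.**

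- d within one group, on the SD of change: t(0.975, 21)/√22 = 0.443.
- Time effect over all 44 women: 2.017/√44 = 0.30.
- Between-group test on change scores with d on the raw-score SD: 0.608 × √(2(1 − ρ)). This is 0.47 at ρ = 0.7 and 0.38 at ρ = 0.8, and drops below 0.50 once ρ exceeds about 0.66. The baseline-to-final correlation ρ is an assumption, since the article gives none.

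**The case against.** A reader might infer that every reported effect is inflated. The figures do not support that. The bias is an average and fades as the true effect grows; from a true d of 0.8 upward, 31% to 49% of significant estimates lie below the truth. The only effect the article quantifies, 69% against 13% improved, corresponds to a d of about 1.5 to 1.6 on a latent logistic or normal scale (an assumption about scale), and there the filter is harmless. Small values of d remain fair to consider, because Objectives {7} predicts no difference between groups.

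A reader might also infer that no d in the trial can be graded low. That holds only for the between-group d on the pooled SD of the tested variable. Section {20a} does not confine d to that comparison or name the SD. Since both groups are expected to improve, pre-post differences may well be significant, and a within-group d can fall between 0.44 and 0.49.

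Nor does the rule hide all information on non-significant outcomes. Section {20a} describes means with SDs, or medians with interquartile ranges, whatever the p-value. A reader could rebuild a between-group d from the group means and SDs of the variable tested.

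Finally, a minimal important difference may be left to a fuller document that is not shown, so its absence is not the point here. The rule also leaves the randomisation, the data and the primary p-value untouched.

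These limits stand. They do not rescue the significance condition or the use of d to confirm relevance, which are stated choices rather than omissions.

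**Conclusion.** The point holds in a bounded form. Conditioning Cohen's d on significance gives a between-group floor of 0.61 at 22 per arm, so the low class is empty for that comparison. Mean reported |d| is 0.76, 0.78 or 0.83 when the truth is 0.2, 0.3 or 0.5; the excess is about 0.15 at 0.8 and negligible at 1.5. If the authors' prediction of no difference is right, about 95% of between-group comparisons receive no effect size.

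This rests on 22 analysed women per arm, approximately normal data, a 0.05 threshold and d on the pooled SD of the variable tested. It concerns interpretation and reporting, not the validity of the primary test. It is worth correcting because the remedy is nearly free.

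**What to change.** In {20a}, delete the condition "based on significant differences" and the statement that d confirms clinical relevance. Suggested replacement:

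*For each outcome, whether or not the comparison is significant, we will report the between-group difference in original units with its 95% CI, and Cohen's d with its 95% CI, standardised by [named SD]. Clinical interpretation of the primary result will be based on the confidence interval in ICIQ-SF points.*

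Preferably, name an ICIQ-SF difference before unblinding against which that interval will be read; this is a useful addition, not a condition of the fix. No covariate adjustment or change to the test is implied.

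The cost is a revised sentence, a few more table columns and some effect sizes that look less favourable. No new data or participants are needed.

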### Interim analyses {21b}

No interim analysis will be performed.

### Methods for additional analyses (e.g., subgroup analyses) {20b}

None planned.

### Methods in analysis to handle protocol non-adherence and any statistical methods to handle missing data {20c}

The analysis will be performed according to the intention-to-treat criteria. Any missing data and the reason for the missing data will be described for each group.

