**Methods:**

This is a prospective clinical study to compare two randomized groups based on parallel and blind conditions. Forty-four women who have had a stroke episode at least 30 days before the trial and who have developed overactive NB will be recruited for the trial. All patients will be subjected to initial evaluation and randomly divided into two groups, TNES and PSES. Subsequently, the two groups will be subjected to a 12-session intervention protocol, twice a week. A new evaluation will be performed after the intervention.

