### Plans to promote participant retention and complete follow-up {18b}

Intention-to-treat analysis will be carried out [31]. Therefore, all participants who discontinue or deviate from the initially randomized intervention will be evaluated. Those participants who discontinue the intervention will receive telephone contact from the researcher after 6 weeks of the first evaluation to attend the laboratory for reevaluation.

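### Intention-to-treat is promised, but no rule says how women without a final ICIQ-SF are analysed, and the named ANOVA has no baseline adjustment, so by default they are left out

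*Protocol article*

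**What the plan says.** The Protocol article promises intention-to-treat in three places.

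- **Retention {18b}:** "all participants who discontinue or deviate from the initially randomized intervention will be evaluated". Women who stop are telephoned six weeks after their first evaluation and asked to come back for reassessment.
- **Statistical methods {20a}:** "The intention-to-treat analysis will be carried out". The only test named is ANOVA between groups, for parametric data. Baseline adjustment is not mentioned.
- **Non-adherence and missing data {20c}:** after repeating the intention-to-treat principle, the section says "Any missing data and the reason for the missing data will be described for each group". Nothing else is said about missing values.

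Three other sections bear on this. Outcomes {12} makes the primary outcome the change in ICIQ-SF from baseline to final evaluation. Participant timeline {13} gives one assessment after baseline. Criteria for discontinuing {11b} names withdrawal of consent as the discontinuation criterion.

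**The concern.** Describing missing data is reporting. It does not say how a randomised woman without a final score contributes to the primary comparison. With one follow-up score, and neither imputation nor a likelihood-based model named, the stated ANOVA can use only women who have both scores. The recall makes that group larger but cannot guarantee that it is everyone: some women will not return, and those who withdraw consent may not be recallable. The section itself provides for missing data.

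Two things are at stake. First, an analysis of returners could be published under the intention-to-treat label. Second, ANOVA without baseline adjustment is open to bias if the women lost differ in baseline severity between arms. The stated hypothesis is that the groups will not differ, so the reader must be able to see that the result does not depend on who came back.

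**Working it through.** **1. The plan's own figure.** Sample size {14} uses "considering a confidence of 99%, a power of the test of 90" percent, "improvement after TNES of 69% (PA = 0.69") and "patients who had improvement after PSES of 13% (PB = 0.13"), and concludes that "the sample size for each group was 22 women". With p̄ = (0.69 + 0.13)/2 = 0.41:

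n = [z_α√(2·0.41·0.59) + 1.282·√(0.69·0.31 + 0.13·0.87)]² / 0.56²

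- Two-sided α = 0.01: (2.576·0.696 + 1.282·0.572)²/0.3136 = 20.3, so 21.
- One-sided α = 0.01: 17.6, so 18 without continuity correction and 22 with it.

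The 22 is reproduced. The Abstract's total ("Forty-four women who have had a stroke episode at least 30 days before the trial") is 2 × 22, so nothing is added for loss. Power is not the issue here. The figure only shows that every non-returner comes out of the 22.

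**2. What the stated test can use.** Change score = final − baseline, so without a final score there is no change score. ANOVA on final scores has the same limit. A repeated-measures ANOVA on two visits tests the same contrast as change and also needs both scores.

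**3. Size of the bias when loss depends on baseline.** The protocol gives no loss rate, correlation or ICIQ-SF standard deviation, so these are assumptions and results are in SD units. Assume no true difference, 22 per arm, and baseline–final correlation ρ from 0.3 to 0.7. The probability of loss has logit −2.2 in arm A (10%) and −1.5 + 1.2 × baseline z-score in arm B (about 23%).

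In arm B, the mean of z × P(loss) is 0.175 and mean loss is 0.235. The mean baseline of returners is therefore −0.175/(1 − 0.235) = −0.228 SD; in arm A it is 0. Call this difference d = −0.228. Then:

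- bias of ANOVA on change = −(1 − ρ)·d
- bias of ANOVA on final score = ρ·d

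| ρ | Bias, change | Bias, final | SE, change | SE, final | Bias, ANCOVA | ANCOVA SE vs change |
|---|---|---|---|---|---|---|
| 0.3 | +0.16 | −0.07 | 0.39 | 0.33 | under 0.005 | 16% smaller |
| 0.5 | +0.11 | −0.11 | 0.33 | 0.33 | under 0.005 | 10% smaller |
| 0.7 | +0.07 | −0.16 | 0.26 | 0.33 | under 0.005 | 5% smaller |

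Standard errors and ANCOVA results come from simulation (8,000 replicates per row), which also reproduced both bias columns to within 0.01. Higher ICIQ-SF is worse, so the arm losing its severe women looks worse on change and better on final score. The largest bias is about half a standard error (0.16/0.33 = 0.48). The type I error of the unadjusted tests was between about 5% and 8%, against a nominal 5%.

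**4. Less adverse patterns, same ρ range.**

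- Same mechanism in both arms: bias at most 0.01 SD.
- Loss of 10% and 23%, unrelated to baseline: zero apart from simulation noise (at most about 0.02 SD).
- Loss of 10% and 23%, same moderate slope (0.6) in both arms: about 0.02–0.06 SD.

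**5. Precision without differential loss.** The large-sample reduction in standard error from ANCOVA relative to change is 1 − √((1 + ρ)/2), which is 19%, 13% and 8% for ρ = 0.3, 0.5 and 0.7. Simulation with 22 per arm and no loss gave 19%, 12% and 6%.

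**6. What baseline adjustment cannot remove.** If loss depends on the unseen final score, bias = (difference in loss) × (non-returners minus returners), taking that gap as equal in both arms. For 10% against 30% loss and a gap of 0.5 SD: 0.20 × 0.5 = 0.10 SD.

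**The case against.** A reader might infer that the protocol prescribes a complete-case analysis, or that its intention-to-treat claim is false. The documents support neither. No section says that women without a final score are excluded, and describing missing data rules out no method. ANOVA is fixed only for parametric data, and {20a} does not say which scores enter it. The full protocol, an analysis plan or the reference cited for intention-to-treat may settle the handling, and an article may leave imputation details there. The article also does provide for the core of intention-to-treat: women are followed up whatever their adherence, with a recall. All of this stands, which is why the point is limited to what happens by default to women still missing after recall.

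A reader might also infer that the result will be biased by 0.1–0.2 SD. That is not supported either. It takes loss that is both unequal and tied to baseline severity in one arm, at assumed rates, and even then the bias is below one standard error.

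Finally, the gain in the table comes from baseline adjustment and not from imputing scores: ANCOVA on returners alone already removes the bias. That is correct, and it sets the order of the remedies.

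What the objection does not remove is that the article has a section for this item and answers it with a reporting commitment beside an intention-to-treat claim. It also names a test that makes no use of the baseline score as a covariate, although that score is already collected.

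**Conclusion.** The point holds in limited form. As written, women still lacking a final ICIQ-SF after recall would by default fall out of the primary comparison, and the intention-to-treat label is not backed by a rule for them. The resulting bias is modest: up to about 0.16 SD in an adverse scenario of 10% against 23% loss tied to baseline severity in one arm, near zero in benign ones, and below one standard error in every baseline-dependent scenario examined. Its direction depends on whether change or final score enters the ANOVA. Loss rates, correlation and mechanism are assumptions. The case for changing the plan rests as much on precision, which improves whether or not loss is unequal, as on bias.

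**What to change.** **Statistical methods {20a}.** Replace the ANOVA for the primary comparison with a baseline-adjusted model. Either of these would do:

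- ANCOVA of final ICIQ-SF on group and baseline.
- A linear mixed model on baseline and final scores of all randomised women, with one common baseline mean for both arms. If the baseline means are left free, the bias still goes but the precision gain is largely lost (at ρ = 0.3 the simulated standard error was 0.38, against 0.39 for change scores).

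**Missing data {20c}.** State that women without a final score enter through the mixed model, or through multiple imputation from baseline and group followed by ANCOVA. Reason for stopping should not be an imputation variable, since it is undefined for women who complete treatment. Add one simple sensitivity analysis that varies the missing scores. If only returners are analysed, describe the result as an analysis of available cases as randomised.

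The cost is a few sentences and slightly more analysis work. No new data are needed, and these are standard procedures in the named software.

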### Plans to give access to the full protocol, participant-level data, and statistical code {31c}

The datasets analyzed during the study will be available from the corresponding author upon reasonable request.

## Oversight and monitoring

### Composition of the coordinating center and trial steering committee {5d}

The researchers involved in the study (see on the title page) form the coordinating center responsible for study coordination, monitoring, data acquisition and management, and statistical analysis.

### Composition of the data monitoring committee, its role, and reporting structure {21a}

This study will not have a data monitoring committee, as it is a short-term trial with minimal known risks.

### Adverse event reporting and harm {22}

This study involves minimal known risks but, daily, the researcher responsible for the interventions will question the participants about possible adverse effects. It is possible to complain of skin irritation due to the electrode fixation or even increased symptoms. Any harm detected will be reported to the institution’s research ethics committee.

### Frequency and plans for auditing trial conduct {23}

No audits are planned because this trial is academic.

### Plans for communicating important protocol amendments to relevant parties (e.g., trial participants, ethical committees) {25}

According to national regulations, major modifications of the protocol require a formal amendment to the protocol and are to be approved by the institution’s research ethics committee and modified in the Brazilian Registry of Clinical Trials.

### Dissemination plans {31a}

The trial results will be submitted for publication in relevant journals and presented at conferences in the area of physiotherapy and urology. In addition, the results will be published on the university’s social media using accessible language so that it is known to the population.

## Discussion

Electrostimulation techniques are widely used to treat UI [33] and, in Brazil, it is often used by physical therapists in their clinical practice. However, studies about the herein assessed specific population—women with overactive NB after a stroke episode subjected to the parasacral technique—were not found. Only one study involving a sample of 4 women subjected to the tibial nerve technique was found in the literature [16]. There are no clinical essays based on the protocol and that have compared the effects of these two techniques in this population. Accordingly, the results of this first study with the application of these techniques in the population of women after a stroke are able to assist the clinical decision-making of physical therapists. As a technique with low cost, no side effects, and good adherence of patients [6], electrostimulation can assist in reducing urinary complaints of patients. Moreover, these results can contribute to new studies based on comparing treatment techniques to improve the quality of life of these patients.

### Trial status

The study was registered at the Brazilian Registry of Clinical Trials (REBEC) (number RBR-2bn2z4) on December 11, 2018. Recruitment began on January 09, 2019. For organizational issues of intervention services in women after strokes, it was necessary to conduct the recruitment of volunteers before sending the protocol. The study was interrupted due to the COVID-19 pandemic, and recruitment is expected to be completed by 2021.

## Abbreviations

ANOVA: Analysis of variance
F: Frequency
ICIQ: International Consultation on Incontinence Questionnaire-Short Form
MMSE: Mini-Mental State Examination
NB: Neurogenic bladder
PSES: Parasacral electrostimulation
REBEC: Brazilian Registry of Clinical Trials
SPIRIT: Standard Protocol Items: Recommendations for Interventional Trials
T: Pulse length
TNES: Tibial nerve electrostimulation
UI: Urinary incontinence
WHOQOL-BREF: World Health Organization Quality of Life – BREF
